**Methods:**

The longitudinal quasi-experimental study will be undertaken in two purposively selected blocks of one district each in the four intervention states and one comparison state. From each state, 200 SAM children identified using weight-for-length/height z-score (WHZ) < **−** 3 criteria will be enrolled in the study. Their anthropometric data and skinfold thickness will be taken on admission, at sixth week and at discharge by trained field investigators. Other child details, incidence of morbidity and socio-economic details will be collected on admission. To assess food consumption pattern including consumption of locally produced nutrient dense food supplements, dietary assessment, using 24-**h** dietary recall will be conducted on admission, at sixth week and at discharge. In addition, body composition parameters will be assessed for a sub-set of children using bio-electrical impedance analysis on admission and at discharge to analyse changes in total body water, fat-free mass, and fat mass. Post discharge, all study participants will be followed up monthly until 6 months. Atleast 10% of the sample will be checked for quality assessment.

The study’s primary outcome is cure rate defined as children attaining WHZ **≥** -2. Secondary outcomes include mean weight gain, mean length of stay, body composition parameters, relapse and mortality rates. Additionally, process evaluation and cost effectiveness analysis will be conducted.

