### Study design and setting

This multi centric longitudinal quasi-experimental study with a comparison area will take place in two blocks each in Gadwal (state Telengana), Hoshangabad (state Madhya Pradesh), Rajnandgaon (state Chhattisgarh), Nabrangpur (state Odisha) and Latehar (state Jharkhand) districts. More than 80% population in these districts reside in rural areas with more than one-third of the households being poor [25]. The prevalence of wasting and severe wasting among children in these districts are very high. Wasting among children under five in these districts are 18.6, 29.6, 17.2, 36.0 and 29.0% respectively and severe wasting prevalence is5.1, 10.6, 6.2, 11.6 and 10.7% respectively [4]. From each of the four intervention districts, two study Blocks will be purposively selected where either the CSAM intervention is currently being implemented or have been planned by the respective state governments. Similarly, two study Blocks from Latehar district of the state Jharkhand will be purposively selected as comparison area, where no CSAM intervention is being implemented.

The study will be led by Kalawati Saran Children’s Hospital (KSCH), New Delhi and supported by Children’s Investment Fund Foundation (CIFF) through UNICEF, India. KSCH will partner with Indian Council of Medical Research-National Institute of Nutrition (ICMR-NIN), Telangana, All India Institute of Medical Science (AIIMS) in Madhya Pradesh and Chhattisgarh, National Health Mission (NHM) of Odisha and Rajendra Institute of Medical Science (RIMS), Jharkhand, who will administer and manage the study in the respective states.

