### Data analysis

Final analysis will include all children enrolled in the study. Appropriate quantitative analyses will be used including descriptive statistics (proportion, percentage, mean or median), comparison of difference in proportion for binary outcome using Pearson chi-square and comparison of average change for continuous variable using t-tests. Recovery will be compared for effectiveness of state specific CSAM protocols and locally produced nutrient dense food supplements in four intervention states in comparison to the comparison state. Cox regression method will also be used for this analysis by defining recovery as event, as it can utilize the entire sample size including defaulters or loss to follow up. Other parameters including skinfold, defaulting, death, length of stay, average weekly weight gain and height gain will also be compared between the intervention states and the control state. Subgroup analysis will be done for comparing recovery among children aged 6–23 months and 24–59 months between intervention states and control state. For the sub-sample of body composition, change in fat mass, fat free mass and body water will be compared between the four intervention states and the comparison state. A linear mixed model will be developed for different outcomes (recovery, weight gain, and body composition parameters) adjusting for various random and fixed effects across all sites adjusted for differences at baseline.

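### Recovery has three listed analyses and none is named as primary, so an unadjusted chi-square that ignores clustering could supply the main answer of a non-randomised study

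*Protocol article*

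**What the plan says.** The primary outcome is binary: the abstract's Methods state that the "primary outcome is cure rate defined as children attaining WHZ" of at least -2. The design is not randomised. Study design and setting says "This multi centric longitudinal quasi-experimental study with a comparison area will take place in two blocks each" in one district of each of five states, and "two study Blocks from Latehar district of the state Jharkhand will be purposively selected as comparison area". The intervention blocks are also chosen purposively.

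Data analysis then names three methods that apply to recovery:

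- "comparison of difference in proportion for binary outcome using Pearson chi-square", with no covariates and no allowance for clustering;
- "Cox regression method will also be used for this analysis by defining recovery as event", with no covariates or cluster term stated;
- "A linear mixed model will be developed for different outcomes (recovery, weight gain, and body composition parameters"), described as "adjusting for various random and fixed effects across all sites adjusted for differences at baseline".

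The section does not say which of the three answers the primary research question. The Sample size section plans for cure of 50% against 25%, with a design effect of 1.5.

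**The concern.** Where areas are chosen rather than randomised, a crude difference in cure mixes the programme effect with any difference in the children admitted. Admission WHZ matters most, because a child who starts closer to -3 has less far to go to reach -2. The way children are found also differs by arm. Frontline workers identify them in the intervention states and field investigators recheck them, whereas field investigators identify them directly in the comparison state (Selection of study samples). Table 1 gives monthly active screening in Madhya Pradesh and quarterly screening in the other three programmes. These are reasons to expect that admission severity may differ.

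A Pearson chi-square can deal with neither this nor the clustering that the sample size allows for. The analysis stated to be adjusted does exist, but it groups a yes/no outcome with continuous ones under a linear model. With three results available and none ranked, the unadjusted one could be reported as the trial's answer.

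**Working it through.** **1. The plan's own figure.** Inputs from Sample size: cure 50% and 25%, 5% significance (taken as two-sided), 80% power, design effect 1.5, attrition 20%. With unpooled variance:

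n = (1.960 + 0.842)² × (0.50×0.50 + 0.25×0.75) / 0.25² = 54.94, rounded to 55.

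55 × 1.5 = 82.5, and 82.5 × 1.2 = 99, which matches the stated 100 per age group. The design effect is therefore built into the planned size, and the plan itself expects the variance of a cure comparison to be 1.5 times the independent-sample value.

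**2. A plain chi-square under that design effect.** If the true variance is 1.5 times what the test assumes, the 1.960 cut-off acts as 1.960/√1.5 = 1.600. The true two-sided error is 2 × [1 − Φ(1.600)] = 0.110, about 11%. With a smaller design effect of 1.25 (assumed) the cut-off acts as 1.753 and the error is about 8%.

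**3. Cost of the linear form.** Assume five equal states, four at 50% cure and one at 25%. The binomial variances are 0.25 and 0.1875.

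- Pooled residual variance: (4×0.25 + 0.1875)/5 = 0.2375, so an intervention-versus-comparison contrast is given variance proportional to 2×0.2375 = 0.475.
- True value: 0.25 + 0.1875 = 0.4375.
- Ratio of standard errors: √(0.475/0.4375) = 1.042.

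The standard error is about 4% too large, so the test is slightly conservative.

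**4. Size of possible confounding (illustration; inputs assumed).** Take the SD of WHZ change as 0.9 to 1.0 and an admission difference of 0.2 z between two states. The shift in cure is about 0.2 × φ(z_p)/SD:

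| Cure rate | φ(z_p) | SD 1.0 | SD 0.9 |
|---|---|---|---|
| 25% | 0.318 | 6.4 points | 7.1 points |
| 50% | 0.399 | 8.0 points | 8.9 points |

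Against the planned 25-point effect, that is roughly a quarter to a third.

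A second illustration assumes no programme effect and a binary prognostic factor with cure of 50% when present and 25% when absent. If it is present in 60% of children in one state and 40% in the other, cure is 0.25 + 0.25×0.60 = 40% against 0.25 + 0.25×0.40 = 35%, a spurious 5 points. With 200 per state and no clustering, the standard error is √(2×0.375×0.625/200) = 0.0484, and the crude test rejects about 18% of the time.

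**The case against.** The plan already commits to a baseline-adjusted mixed model that covers recovery, and it also names Cox regression, which suits a yes/no event and can carry covariates. The chi-square sits in a general list beside descriptive statistics and t-tests. In a condensed article, linear mixed model may be loose wording for the mixed-model family, and a linear model does estimate a risk difference, the scale of the planned effect. All of this stands. The covariate list may also properly sit in an analysis plan that is not shown, and its absence is not part of this point.

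Three stronger readings are tempting, and the documents do not support them.

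- A reader might infer that the crude test is the intended primary analysis because it is listed first. The text does not rank the analyses.
- A reader might infer that the linear model invalidates the primary result. Step 3 shows a small, conservative error.
- A reader might take the district figures, "severe wasting prevalence is5.1, 10.6, 6.2, 11.6 and 10.7% respectively", as proof of confounding. They describe district populations, while every enrolled child has WHZ below -3. The extremes, 5.1% and 11.6%, are both intervention districts; the comparison district has 10.7%. If WHZ is assumed normal with SD 1.0 to 1.4, these prevalences imply a mean admission WHZ among severely wasted children that differs from the comparison district by 0.06 to 0.09 z in Gadwal, 0.05 to 0.07 z in Rajnandgaon, and about 0.01 z or less in the other two. With the slopes in step 4, that is at most about 2 to 4 points of cure.

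The 11% figure is also conditional. With 200 children from 100 centres, about two per centre, a design effect of 1.5 from centre clustering alone would need an intracluster correlation of 0.5, since 1 + (2 − 1)×0.5 = 1.5. The true value may be lower.

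The objection leaves the main point untouched: the stated methods allow an unadjusted, unclustered test to answer the primary question.

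**Conclusion.** The point holds as a matter of analysis choice and deserves a change before analysis. The main defect is that no analysis of recovery is designated primary while one of the three ignores both baseline differences and the plan's own clustering allowance. If the design effect of 1.5 is right, that test runs at about 11% instead of 5%. The possible bias from admission imbalance is illustrated at about 6 to 7 points at 25% cure and 8 to 9 points at 50%. Those figures rest on an assumed 0.2 z difference and an assumed SD of WHZ change; the documents give neither. The linear form for a binary outcome is a secondary matter.

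**What to change.** Name one covariate-adjusted model for binary cure as the primary analysis, for example a logistic mixed model, or a logistic or modified Poisson GEE, with clustering by anganwadi centre. Adjust for admission WHZ, age, admission morbidity, and household socio-economic and water and sanitation variables. Report an adjusted risk difference for each intervention state against the comparison state. Present the chi-square as descriptive, and keep the linear mixed model for weight gain and body composition.

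State as a limitation that, with a single comparison district, adjustment reduces measured confounding but cannot separate the programme effect from the state effect.

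Before this model can be written, the time point for cure has to be settled. Table 1 gives 12 weeks for Madhya Pradesh and 16 for Chhattisgarh, while Sample size gives 12 for Chhattisgarh and 16 for Madhya Pradesh. The two sections must be reconciled, and the model should not presume a week common to all states.

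Apart from that reconciliation, the cost is wording. The admission measurements and household data are already in Table 2, and the centres are already the sampling units.

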### Process evaluation

A process evaluation will document the design, implementation and mechanisms of the CSAM intervention in the study states to enable replication and scale up. It will use data from the CSAM planning and monitoring document and forms to capture compliance, challenges and learning. Furthermore, semi-structured interviews with state, district and block officials, frontline workers and caregivers and focus group discussions with small family groups and frontline workers will be conducted to document perceptions of the intervention and its effects.

### Cost effectiveness analysis

We will conduct cost and cost-effectiveness analyses to guide policy decisions and inform any subsequent scale up. We will estimate the total and incremental costs of the CSAM intervention in each of the four intervention study states from the provider’s perspective. The costs of delivering the CSAM interventions both at the community and the facility levels will be collected retrospectively from the accounts of government and other partnering institutions, using a standardised data capture tool designed for this purpose in Excel. This will also be combined with key informant interviews and available financial data on the average unit cost of delivering those services. Time use study will be conducted with frontline workers and other key implementers to value their time spent in the CSAM intervention. Cost of any donated resource to the CSAM intervention will also be included in the analysis. All costs will be adjusted for inflation using the Indian Consumer Price Index (CPI) and will be presented in Indian Rupees and 2021 International Dollars. Incremental cost-effectiveness will be measured in relation to the status quo alternative i.e. doing nothing in addition to the current ongoing activities as part of government nutrition promotion initiatives. Incremental cost-effectiveness ratios (ICERs) will be calculated for the primary outcome measures (i.e. SAM cases treated and cured/recovered) and selected secondary outcome measures such as cases of child mortality averted, life-years saved and disability adjusted life years (DALYs) averted. Sensitivity analyses will be carried out to assess the robustness of results.

## Discussion

Different state governments have contextualized, designed and developed operational CSAM protocols for implementing their state specific CSAM strategies to be manageable within their existing NHM and ICDS systems. The study results will be generalisable to rural areas of India with a high burden of childhood wasting and underserved community. There are a large number of high-burden districts and Blocks in India where prevalence of SAM among children is very high. If the CSAM strategies of different states improve the study’s primary and/or secondary outcomes, the intervention strategies can be scaled up to all or parts of the high- burden districts through NHM and ICDS systems. These intervention strategies will also enable the health and ICDS systems to work in collaboration with each other at the village level through their existing frontline workers.

### Trial timeline and status

The trial is planned for a duration of 12 months (1st December 2020 – 30th November 2021) and is currently recruiting participants.

## Data Availability

Not Applicable.

## Abbreviations

SAM: Severe Acute Malnutrition
CMAM: Community-based Management of Acute Malnutrition
WHO: World Health Organisation
CSAM: Community-based Management of Severe Acute Malnutrition
AWC: Anganwadi Centre
WHZ: Weight for Height Z-score
BIA: Bio-electrical Impedance Analysis
TBW: Total Body Water
FFM: Fat Free Mass
FM: Fat Mass
MUAC: Mid Upper Arm Circumference
RUTF: Ready to Use Therapeutic Food
BMI: Body Mass Index
AMA: Arm Muscle Area
AFA: Arm Fat Area
NRC: Nutritional Rehabilitation Centre
IYCF: Infant and Young Child Feeding
THR: Take Home Ration
MTC: Malnutrition Treatment Centre
KSCH: Kalawati Saran Children’s Hospital
CIFF: Children’s Investment Fund Foundation
UNICEF: United Nations Children’s Fund
AIIMS: All India Institute of Medical Sciences
NHM: National Health Mission
RIMS: Rajendra Institute of Medical Sciences
ICMR-NIN: Indian Council of Medical Research-National Institute of Nutrition
PPS: Probability Proportional to Size
TB: Tuberculosis
HIV: Human Immunodeficiency Virus
TEM: Technical Error of Measurement
CPI: Consumer Price Index
ICER: Incremental Cost Effectiveness Ratio
DALY: Disability Adjusted Life Year
ICDS: Integrated Child Development Services
